### Sample size calculation

Sample size calculations refer to a log-rank statistic under *α* = 0.05 and *β* = 0.2 (80% power) under the assumptions of (a) an accrual time of 24 months, (b) a total study duration of 48 months with a primary time point of interest at 18 months post-baseline, and (c) a drop-out rate of 12% (the latter based on experiences from previous studies [2, 3, 5]; and relates to the study observation period of 18 months). We define a treatment effect of factor 2 as a relevant effect, i.e., a hazard ratio (HR) of 0.5, for instance, is regarded as a relevant effect. Previous trials have indicated about 4% of the study population under risk (excluding dropouts) will experience a relapse under conventional therapy each month. HR = 0.5 would require 2% per month for the SECT group and a study population of *N* = 360 patients (180 patients per treatment arm) to reach significance under *α* = 0.05 and *β* = 0.2. The study with a proposed *N* = 300 would require HR = 0.46, and the pessimistic scenario of *N* = 200 would have to reach HR = 0.375. Thus, the study with *N* = 300 intended can yield statistical significance if the treatment effect in the SECT group exceeds factor 2. In addition, our sample size calculation is based on the publication by Jahn-Eimermacher et al. [33] which fits—regarding sample sizes for time-to-event data—the requirements of the present study best and results in an identical sample size.

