### Statistical analysis

The question as to whether specific psychotherapy can prolong the time until relapse will be addressed by non-parametric survival analyses involving log-rank or Wilcoxon statistics and sensitivity analyses for the ITT (intent-to-treat) sample and the PP (per-protocol, required is participating in at least 75% of treatment sessions) sample. The time-dependent evolution of group-specific hazard rates will be investigated by parametric models addressing the differences in the dynamics of relapse in both intervention arms. Cox regressions will be performed to identify the risk factors for the probability of relapse and time until relapse if the proportional hazard assumption will not be negated. Our planned analyses will allow to identify if the types of participants with missing outcomes look different to those observed outcomes and whether this pattern might be different by arm: treatment arm with no missing primary outcome at primary time point, treatment arm with missing primary outcome at primary time point, control arm with no missing primary outcome at primary time point, and control arm with missing primary outcome at primary time point. Secondary endpoints like symptomatology, days missed at work/school, or social functioning level will be described on a univariate level and enter multivariable group comparisons on the base of an ANCOVA (with the factor kind of intervention (2) and time points (2 to 4) using baseline as a covariate) and involve stepwise variable selection. Based on the results for these covariates, methods such as principal component analysis or latent variable modeling will finally be considered to identify the risk factors for the probability of relapse and time until relapse. We have the intention to use the CONSORT statement for reporting the outcome and final results of this randomized controlled trial.

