This study hypothesizes that SECT may be a preferential intervention to EFST. SECT is tailored for bipolar patients based on the existing empirical evidence and clinical factors. However, it should be noted that the intervention in its current form—while considered safe—as of yet lacks empirical support. The monthly workshop format of the intervention is also novel. In other patient groups receiving individual therapy, less frequent sessions appear to impact outcomes negatively (e.g., PTSD and depressed patients, see [34, 35]). However, this may not be the case for patients in remission as has been shown in some studies (e.g., [36]). Indeed, the monthly format is proposed to increase opting-in, particularly for patients living in more rural areas who may have long distances to travel in order to engage in therapy. While therapy is only offered once a month, it should be noted that the “dosage” of therapy is relatively high, with an 8-h day being equivalent to 42-h sessions a week within a month. However, it is ethically notable that participants may not engage in individual psychotherapy external to the study in the 6 months prior to or during the course of the intervention. In instances where patients wish to commence individual psychotherapy during their study participation, patients are free to exercise their right to drop out and are considered to be lost to attrition. Despite this, it cannot be ruled out that patients’ knowledge of these exclusion criteria does not inform their own choice to forgo individual psychotherapy during their participation in the trial.

It is important to acknowledge that as with all RCTs, the current study involved the randomization of patients to either an active or (relatively) passive therapy condition. It is inevitable that clinicians may have an intuition or preference as to which condition may serve the patient’s interests at a given stage in the course of their illness. To eliminate the possibility of such preferential treatment against the interests of the study and research ethics, randomization is blindly completed by the lead study center (who only receives the patient’s age, gender, and number of past episodes to inform the normal distribution of the treatment groups).

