A further concern is the within-group variability, arising from heterogeneity across the spectrum of bipolar diseases. According to previous research [37], different personality styles within major depressive disorder (MDD) have an influence on how patients respond to therapy and whether they adhere to treatment. By distinguishing two personality types within MDD, the authors have shown that patients with increased self-criticism may be inhibited by structured therapies such as cognitive-behavioral therapy. It is quite conceivable that adherence is similarly influenced by different personality types in bipolar disorder. As we compare two different forms of therapy, one more structured (SECT) than the other (EFST), without assessing the personality traits of patients, we cannot report on to what extent there may be a reciprocal influence. In addition, aspects such as variability of group size and the degree of the structure may play a more significant role and may have a negative impact on the outcome. Another limitation may arise from the uncertainty regarding whether patients, despite awareness of the exclusion criteria regarding concurrent individual psychotherapy parallel to the study, may choose to discretely engage in one-to-one therapy, which could influence the results. Furthermore, we do not assess patients’ preceding therapy experiences, which may result in within-group variability: Someone with an initial maniEFSTation and no therapy experience may respond differently to the intervention from someone with accumulated years of therapeutic care. Finally, although there have been various attempts to create uniform conditions across the various study centers, a multicenter study always bears the risk of a certain variability that cannot be ruled out completely.

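### The relapse comparison is an unadjusted two-group test although baseline data are held; a pre-specified covariate-adjusted log-rank test may recover some power and costs almost nothing

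*Protocol article*

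**What the plan says.** All of this is in the protocol article.

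- **Statistical analysis, relapse.** Time to relapse is addressed by "non-parametric survival analyses involving log-rank or Wilcoxon statistics and sensitivity analyses for the ITT (intent-to-treat) sample", and likewise for the per-protocol sample. No covariate is named for this comparison.
- **Statistical analysis, Cox models.** "Cox regressions will be performed to identify the risk factors for the probability of relapse and time until relapse", provided the proportional hazards assumption is not contradicted. Their stated job is to find risk factors, not to give an adjusted treatment effect.
- **Statistical analysis, secondary endpoints.** These go into an ANCOVA "using baseline as a covariate".
- **Ethical issues and considerations.** The lead centre receives each patient's "age, gender, and number of past episodes" when it randomizes, for the sake of an even spread between the groups. The Randomization section lists centre as the only stratification factor.
- **Assessments/measures, Table 1.** SCID, LIFE, YMRS, QIDS-C, ASRM, QIDS-SR, GAF and FAST are all taken at baseline. Bipolar I or II is an inclusion criterion, so the type is known for every patient.
- **Discussion.** "A further concern is the within-group variability, arising from heterogeneity across the spectrum of bipolar diseases".

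**The concern.** In time-to-event data, a two-group test that ignores prognostic baseline variables is generally less powerful than one that uses them. It also does nothing about a chance difference between arms, for example in number of past episodes or residual symptoms. The remission criteria allow residual symptoms to vary (QIDS-C below 10, YMRS below 12).

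The plan adjusts its secondary endpoints but not relapse, which carries the trial's main claim. The variables needed are already collected, so adjusting requires no new data and no further patients.

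**Working it through.** **1. Inputs from the Sample size calculation section.** The test is a "log-rank statistic under *α* = 0.05 and *β* = 0.2 (80% power"); a two-sided level is assumed, since sidedness is not stated. The control rate is "about 4% of the study population under risk (excluding dropouts) will experience a relapse under conventional therapy each month". Dropout is 12% over 18 months, and the planned N is 300. The relevant effect is a hazard ratio (HR) of 0.5.

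**2. The plan's own figure.** It states "HR = 0.5 would require 2% per month for the SECT group and a study population of *N* = 360 patients".

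- Events (Schoenfeld): d = 4(1.960 + 0.842)² / (ln 0.5)² = 4 × 7.85 / 0.480 = 65.3, so 66.
- 18-month event probabilities: 1 − exp(−0.04 × 18) = 0.513 and 1 − exp(−0.02 × 18) = 0.302, mean 0.408.
- N = 66 / 0.408 = 162 before dropout, and 162 / 0.88 = 184 after.

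The stated 360 does not reproduce; the inputs give about half of it. That is a separate matter, but it sets the starting point here.

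**3. Unadjusted power at N = 300 and HR 0.5.** Expected events run from 300 × 0.408 × 0.88 = 107.7 to 117.3 (dropout as a competing exponential, monthly hazard −ln 0.96). Power = Φ(½√d × 0.693 − 1.960):

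- d = 107.7: Φ(1.64) = 94.9%
- d = 117.3: Φ(1.79) = 96.4%

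Little room is left for a gain at HR 0.5.

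**4. Gain from adjustment, by simulation.** N = 300, exponential event times, control 18-month relapse 1 − 0.96¹⁸ = 0.52, 12% exponential dropout, 1,500 trials per cell. The adjusted analysis is a Cox model with six separate baseline terms, so the cost of estimating them is counted. The SD of the combined baseline log-hazard is an **assumption**, because the document gives no value. The HR is the within-patient-type HR. Cells show power in percent, unadjusted → adjusted.

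| HR | SD 0 | SD 0.3 | SD 0.5 | SD 0.7 |
|---|---|---|---|---|
| 0.50 | 95 → 95 | 95 → 96 | 94 → 95 | 91 → 96 |
| 0.60 | 81 → 81 | 81 → 82 | 76 → 80 | 72 → 82 |
| 0.65 | 68 → 68 | 64 → 65 | 61 → 66 | 57 → 69 |

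A second run of 3,000 trials per cell at HR 0.50 gave about 95/93/92 → 96/96/96 for SD 0.3/0.5/0.7, a gain of roughly 1 to 4 points. The 5-point gap in the table's SD 0.7 cell is within rounding and simulation error: the standard error of a power of 0.91 from 1,500 trials is √(0.91 × 0.09 / 1500) = 0.7 points. With no true effect, false positives in SECT's favour were 1.9 to 3.1% with and without adjustment (nominal 2.5%).

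**5. A different calibration.** This holds the 18-month risks at the protocol's values (HR 0.5) and varies the log HR per SD of one score, 6,000 trials per cell. Power is 95.7 → 95.6 (0.2), 96.0 → 97.0 (0.4) and 96.3 → 98.6 (0.7), a gain of 0 to about 2 points.

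**6. Limits of the simulations.** The adjusted test simulated was a Cox Wald test under proportional hazards. A covariate-adjusted log-rank test tried in the set-up of step 4 recovered most of the gain, but fell somewhat short of it at SD 0.7 with the weaker effects. The upper ends above are therefore best read as ceilings.

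**The case against.** - **Validity.** The log-rank test is a standard choice. It keeps its type I error under randomization and is the test the trial was sized on. This stands: the plan contains no error on this point.
- **Left to the analysis plan.** An analysis plan not shown may add covariates. That is possible, but the article does more than stay silent: it names the relapse test and gives the Cox models a different job. The point is a better method than the one stated, not a missing detail.
- **Prognostic strength is not shown.** This stands. The Background links younger age and few episodes to better effects of psychotherapy, which is effect modification and not prognosis for relapse. The heterogeneity in the Discussion is illustrated mainly by factors the trial does not measure, such as personality style and earlier therapy. Eligibility narrows age and symptom scores. An SD of 0.7 means a hazard ratio of exp(1.4), about 4, between patients 1 SD above and 1 SD below the mean, and nothing in the document supports that strength.
- **Balance may already be sought.** The lead centre receives age, gender and number of episodes for that purpose. However, the Randomization section describes stratification by centre only, so balance on them is not assured.
- **The secondary-endpoint parallel is loose.** The ANCOVA presumably uses each measure's own baseline value, which relapse does not have. The contrast shows an inconsistency of approach, not a contradiction.
- **A Cox model as the main analysis has a price.** It relies on proportional hazards, which the article leaves open, and treatment ends by about month 5 of an 18-month window. Its HR is conditional on the covariates. This stands, and it is why the fix uses an adjusted log-rank test.

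**Conclusion.** The point holds as an improvement, not as a fault that invalidates the analysis. The stated relapse comparison uses no baseline information, and a pre-specified adjusted test would be at least as good under every assumption examined. For an assumed prognostic SD of 0 to 0.7 at N = 300, the gain is about 0 to 4 points of power at HR 0.5 and about 0 to 12 points at HR 0.60 to 0.65. At SD 0.3 it is only 1 to 2 points. HR 0.60 and 0.65 are not in the document; they stand for an effect weaker than the one planned, against an active comparator similar in format and delivery.

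A reader might infer three stronger things that the document does not support:

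- **That substantial power is given away for nothing.** At the protocol's own effect size, unadjusted power is already about 91 to 97% across the simulated scenarios, and the prognostic strength is unknown.
- **That adjustment makes good a shortfall from 360 to 300 patients.** If 360 were truly needed for 80% power, N = 300 would have about 72% at HR 0.5, and the simulated gain would be 0 to about 15 points (log HR per SD 0.2 to 1.0). But 360 does not follow from the stated inputs.
- **That the unadjusted result is biased.** Attenuation relative to a conditional HR mainly reflects non-collapsibility of the hazard ratio; the marginal comparison remains valid.

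**What to change.** Before unblinding, specify:

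1. A short fixed covariate set: number of past episodes, bipolar I or II, baseline QIDS-C, baseline YMRS, age and gender, with no variable selection.
2. A covariate-adjusted log-rank test with that set as the main ITT relapse comparison.
3. The unadjusted log-rank test reported alongside it.
4. An adjusted Cox hazard ratio as the effect estimate where proportional hazards is tenable, with a statement that it is conditional on the covariates.

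The cost is wording in the analysis plan. No new data, visits or patients are needed, and if the covariates turn out not to predict relapse the simulations show essentially no loss of power. What does change is that the main test is no longer exactly the one used for sizing, and that readers need the conditional meaning of the hazard ratio explained.

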### Assessments/measures

Four testing occasions will take place across this longitudinal study, with follow-ups at 5 to 6 months (i.e., immediately post-intervention) and again at 12 and 18 months post-baseline, whereby 18 months follow-up is the primary time point of interest. At baseline, participants’ bipolar disorder is diagnosed by using the Structured Clinical Interview for DSM-IV (structured clinical interview for DSM-IV, SCID 5, German version [23];) with a modified section to assess affective syndromes in line with DSM-V. Current episodes are assessed objectively and subjectively using the Young Mania Rating Scale (YMRS) [24], the Altman Self-Rating Mania Scale (ASRM) [25], and the Quick Inventory of Depressive Symptomatology clinician and self-report forms (QIDS-C, QIDS-SR) [26]. The Global Assessment of Functioning (GAF) [27] and Functional Assessment Short Test (FAST) [28] assess participants’ global social functioning. All measures are administered in the German language and are proven valid and reliable in the German version. The multiple-choice vocabulary intelligence test (“Mehrfachwahl-Wortschatz-Intelligenztest”; MWT) [29] is used as a measure of premorbid IQ. The Longitudinal Interval Follow-up Evaluation (LIFE) (DSM-IV version; developed by Keller et al. [30] and adapted in German for the current study, 2005) is additionally implemented as a key measure in assessing functioning and symptoms in bipolar disorder over time. Following the intervention, therapy satisfaction is assessed using nine items across a 4-point Likert scale using questions such as “The therapy I participated in was of a high quality.” Table 1 gives an overview of the assessment battery as implemented across measurement occasions.

**Table 1 Tab1:** Schedule of enrollment, interventions, and assessments

	Study period					
	First contact	Baseline/randomization	Intervention	Post-assessment	Follow-up 1	Follow -up 2
**Time point**	***Day 1***	***Days 1 to 28***	***Months 2 to 5***	***Months 5 to 6***	***Month 12***	***Month 18***

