### Primary and secondary outcome measures

To examine the effect of the psychotherapy groups, the trial entails one primary outcome measure (relapse) and several secondary outcome measures: time to relapse (LIFE), relapse rate (LIFE), days missed at work/school (record, interview), and social functioning level [32].

Relapse is defined as the development of a new affective (either depression, [hypo] mania, or mixed) episode that meets the diagnostic criteria or results in a hospital admission. Relapse will be assessed every 6 months using the structured LIFE interview (at t2 [end of treatment], t3 [6 months after t2], and t4 [12 months after t2]). The LIFE leads to reliable information regarding the progression and course of illness, time in remission, development of new affective episodes (relapse), and also other mental disorders (co-morbidity). For example, patients are asked at t2, t3, and t4, “The last time we spoke you reported … [description of affective state at the time, e.g., ‘very depressed with problems sleeping’] … How has it been since then? … Since when have you been feeling better/worse?” This is followed with a formal rating based on DSM criteria (“Psychiatric Status Rating”) making note of when the change occurred (“Change Points”) leading to the collection of weekly ratings for the episode. Patients are encouraged to be specific regarding the changes. The interviewer facilitates this by asking questions such as “Was that in November?” and “Did that happen before or after the holiday season?”

Measurements of symptomatology (QIDS-C/SR, YMRS, ASRM), social functioning, and quality of life are assessed to integrate the patient’s everyday perspective (FAST).

Assessment of these outcomes as indicated by changes in these measures over time allows us to address our main hypotheses, i.e., whether SECT versus EFST shows reduced relapse rates, less missed days from work/school, less days spent in the hospital, lower health costs, improved treatment compliance, higher social functioning, and improved neurobiological functioning.

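### Stepwise selection is tied to the secondary arm comparisons without protecting the treatment term, and the ANCOVA wording leaves the within-patient error term open

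*Protocol article*

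**What the plan says.** The Statistical analysis section of the protocol article begins the plan for secondary outcomes with "Secondary endpoints like symptomatology, days missed at work/school, or social functioning level will be described on a univariate level". The same sentence then sends them into "multivariable group comparisons on the base of an ANCOVA (with the factor kind of intervention (2" levels) and, as the second factor, "time points (2 to 4) using baseline as a covariate) and involve stepwise variable selection". The next sentence turns to risk factors for relapse: "Based on the results for these covariates, methods such as principal component analysis or latent variable modeling will finally be considered".

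The section gives no entry or removal rule, does not say that treatment stays in the model, and does not call time a within-patient factor. It also does not say that visits are treated as independent.

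Under Assessments/measures, "Four testing occasions will take place across this longitudinal study": baseline (t1) and three later visits (t2, t3, t4). The same section says that "18 months follow-up is the primary time point of interest". Under Primary and secondary outcome measures, the secondary measures carry comparative weight: "Assessment of these outcomes as indicated by changes in these measures over time allows us to address our main hypotheses", and the list that follows sets SECT against EFST on missed days, hospital days, costs, compliance and functioning.

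**The concern.** In a randomized comparison the covariates should be fixed before the outcomes are seen. Here a data-driven procedure is attached by name to the group comparisons, not only to the later risk-factor work. Read literally, treatment is one of the candidate terms. An arm difference could then disappear from the report because it was not selected, or appear only because it passed a significance threshold.

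The second issue is the time factor. Each patient contributes up to three correlated post-baseline records, and the wording fits analyses that behave very differently. One understates the standard errors. Another is valid with complete data but discards incomplete patients. The range 2 to 4 is itself unclear: it may mean visits t2 to t4, or two to four levels. As only three post-baseline visits exist, a fourth level would make baseline both an outcome and a covariate.

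At stake are the claims that SECT improves symptoms, functioning and missed days relative to EFST. The primary relapse analysis (log-rank or Wilcoxon) is not touched.

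**Working it through.** The article states no figure for the secondary analysis, so there is none to reproduce. The check asks what each reading of the wording would do.

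**Inputs from the article.** N = 300 and 12% dropout over 18 months (Sample size calculation), so 300 × 0.88 = 264 completers and 36 patients lost. Alpha is 0.05, given there for the "log-rank statistic under *α* = 0.05". Up to T = 3 post-baseline visits.

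**Assumptions.** Two-sided test, equal arms, and a constant correlation ρ between any two visits of a patient. The article gives no value for ρ.

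**1. Stepwise selection, one outcome per patient.** Forward selection at p < 0.05 was simulated under no treatment effect, with 264 patients and 1,500 runs per setting.

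| Candidate covariates | Treatment | Treatment effect reported | Type I error | 95% interval covers zero, when reported |
|---|---|---|---|---|
| 10 | always kept | 100% | 4.8% | 95.2% |
| 20 | always kept | 100% | 5.7% | 94.3% |
| 10 | open to selection | 4.6% | 4.6% | 0% |
| 20 | open to selection | 4.0% | 4.0% | 0% |

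The simulation error at 5% is √(0.05 × 0.95 / 1500) = 0.6 percentage points, so the first two rows are compatible with nominal. In the last two rows the false-positive rate is not raised. What fails is the estimate and its interval: a term that enters only at p < 0.05 has an interval that excludes zero when it enters.

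**2. Visits analysed as independent rows.** The variance of the arm effect is understated by D = 1 + (T − 1)r, where r is the correlation between visits after adjustment for baseline. Type I error is then 2[1 − Φ(1.96/√D)].

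(a) If ρ is the raw correlation and also holds with baseline, r = (ρ − ρ²)/(1 − ρ²) = ρ/(1 + ρ). For T = 3:
- ρ = 0.3: r = 0.231, D = 1.462, type I error 10.5% (simulated 9.6%)
- ρ = 0.5: r = 0.333, D = 1.667, type I error 12.9% (simulated 13.3%)
- ρ = 0.7: r = 0.412, D = 1.824, type I error 14.7% (simulated 14.2%)

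(b) If the correlation that remains after baseline adjustment is itself 0.4, 0.5 or 0.6, then D = 1.8, 2.0 or 2.2. Type I error is 14.4%, 16.6% or 18.6% (simulated 15.0%, 16.5% and 17.6%).

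Together these give roughly 10% to 19%. With two visits and version (a), D = 1.231, 1.333 and 1.412 give 7.7%, 9.0% and 9.9%. Forward selection from 15 noise covariates on top of independent rows, under version (b), gave 15.4%, 18.3% and 21.1%.

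**3. Repeated-measures ANCOVA, patient as the error unit.** With complete data and the correlations in (a), simulated type I error was 4.3% to 5.4% (two or three visits, 3,000 runs per setting). This is nominal. The classical form needs every visit, however. If dropouts miss the last visit, at least 36 of 300 patients are left out, plus any who miss a single earlier one. Under Ethical issues and considerations, patients who wish to start individual psychotherapy may drop out and are counted as attrition. That reason may relate to outcome and may differ by arm. The simulation used complete data and does not measure any resulting bias.

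**The case against.** The strongest reply is that the article never says rows are independent. An intervention-by-time ANCOVA in a study it calls longitudinal may well be a repeated-measures ANCOVA, which holds its error rate. Error term, covariance structure and handling of missed visits are details that an article commonly leaves to the full plan. This stands. A reader might infer that the plan mishandles repeated measures and that its p-values and intervals are invalid, but the text does not support this. The 10% to 19% describes one possible reading under assumed correlations.

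A reader might also infer that stepwise selection by itself ruins the tests. With treatment kept in the model it does not: error is 4.8% to 5.7% and coverage 94% to 95%.

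Nor does the article say that only an effect pooled over t2 to t4 will be reported. A time factor allows contrasts by visit, so the fair statement is that no month-18 contrast is tied to the secondary scales.

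Finally, the sentence on risk factors shows that part of the modelling is exploratory, and only secondary endpoints are involved. That limits the weight of the point. It does not remove it, because the selection is written into the group comparisons themselves. That is a method the article states, not a detail it omits.

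**Conclusion.** The point holds in a limited form and should be acted on. The firm part is that the secondary arm comparisons are tied to stepwise selection, with neither the covariates nor the treatment term fixed. The consequence depends on a choice the wording leaves open. It is small for error rates if treatment is retained, and serious for estimates and intervals if treatment can be dropped.

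The conditional part is the within-patient error term. The result is roughly 10% to 19% type I error under independent rows, or about 5% with complete data under a classical repeated-measures ANCOVA that loses incomplete patients. These figures rest on a two-sided 5% test, a constant within-patient correlation in the assumed range, and 264 analysed patients in the simulations. The primary endpoint is unaffected.

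**What to change.** Analyse the continuous secondary scales with a prespecified mixed model for repeated measures:
- fixed terms for arm, visit, arm-by-visit, baseline value, and centre (the randomization stratum);
- a stated within-patient covariance;
- all available post-baseline visits, t2 to t4, with baseline used only as a covariate;
- the month-18 arm difference as the main contrast.

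Always keep treatment in the model. Remove stepwise selection from every arm comparison, including missed days, and keep it only for the exploratory risk-factor models.

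This changes analysis text only, with no effect on visits, data collection or sample size. The cost is slightly more modelling work and possibly wider intervals.
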